**Figure 2 F2:**
[figure not shown]
Effect size as a function of total sample size for power of 0.80.

**Figure 3 F3:**
[figure not shown]
Proposed Consolidated Standards of Reporting Trials (CONSORT) flow diagram.

For the qualitative component in Phase 2, Braun and Clarke (52) have recommended using sample sizes of 10–20 for a medium scope thematic analysis project. Because this thematic analysis is part of a larger mixed methods study and could, thus, be considered a project of medium scope, 20 families (10 from the experimental group and 10 from the comparison group) will be included in Phase 2.


**Table 1 T1:** Subtle disengagement, potent disengagement, and drowsy cues (34).

Subtle	Potent	Drowsy
Gaze aversion, looking away Hand-behind-head or ears Hand to mouth, eye, ear, or stomach Dull looking face/eye Head lowering Joined hands, self-clasp Lip compression, grimace, or pout Sobering, tongue show, ugh face Cling posture, diffuse body movements Facial grimace Frown or brow lowering Finger extension Yawn Rapid wrist rotation Wing palm	Back arching Halt hand Pushing or pulling away Crying, cry face Maximal lateral gaze aversion Overhand beating	Variable activity Irregular respirations Opens and closes eyes Eyes glazed, heavy-lidded look Delayed responsiveness

#### Comparison Group

The comparison group will also receive an intervention during a home visit. The comparison intervention consists only of the individualized review of the standard public health handouts on infant sleep with both parents, based on the parents’ most pressing sleep-related concerns. This discussion will take approximately 30 min. Although each parent in the comparison group will be video-recorded engaging in a play session to capture baseline and outcome parent–child interactions, they will not receive any feedback or review of the video recording. Instead of completing reviews of the video-taped play session, the home visitor proceeds directly to the discussion with both parents of the standard public health handouts on infant sleep. Thus, the comparison group home visit lasts approximately 1 h, which is about the same length of time for the intervention group.

#### Discontinuing or Modifying Allocated Interventions

Given the brevity of the intervention, situations that require discontinuing or modifying the allocated intervention are expected to be rare. In cases of family illness or acute parental mental or physical health concerns, the home visit will be either rescheduled or discontinued altogether, according to family preference. Families who discontinue will be offered a listing of local community health services to which they can self-refer.

#### Adherence

Strategies to increase adherence to study intervention protocols include the use of the same home visitor ([name]) for baseline home visits. As the intervention is concentrated in one home visit and relates to increasing parental ability to read and respond to their infant’s sleep and social cues, no additional adherence strategies will be used. Families will be allowed to contact the home visitor if they require clarification about the information provided during the home visit.

#### Concomitant Care

Families in both groups will not be restricted to using only the sleep strategies or suggestions received during the home visit. Rather, the baseline and outcome questionnaires will collect information about any additional strategies, resources, or services parents use.

#### Blinding

Given that the same home visitor will conduct both the experimental and comparison interventions, the home visitor cannot be blinded to group. Participants will be partially blinded by being informed that the research study is testing two different types of information about infant sleep during the home visit to see which one is superior. In addition, both groups will complete the PCITS protocol as an indicator of the quality of parent–child interactions, which requires parents to engage in a brief structured play interaction with their child. Blinding to group will occur during coding of parent–child interaction videos and data analysis. Given the brief and low-risk nature of the intervention, there are no anticipated circumstances under which unblinding will be required.

### Equipment

A PCITS kit,^1^ along with a digital video camera (Sony HDR-XR350 Handycam Camcorder) and adjustable tripod will be required for the home visits. In addition, a monitor (Sharp LC-13E1U television monitor) that connects to the video camera to play back the digitally recorded play sessions will be used. For the family interviews, a digital voice recorder (Sony IC recorder ICD-SX68) will be used to audio record the interviews.

### Measures

The primary infant sleep outcome will be the frequency of night wakings, as measured by the expanded version of the Brief Infant Sleep Questionnaire [BISQ (48, 53)]. The BISQ is not a psychometric scale, but a screening questionnaire that can be used in clinical practice and research. The expanded version of the BISQ is a multi-dimensional 32-item screening tool (53) developed from the well-established original 13-item tool (48, 54). The original and expanded BISQ both include items covering the domains of sleep ecology, infant sleep patterns, and caregiver perception of infant sleep. However, using the expanded version of the BISQ addresses limitations of previous studies where unspecific and incomplete information on daytime sleep, longest consolidated period of sleep, and sleep ecology, all of which may influence the families’ subjective perception of the presence of sleep problems (53). Given that the BISQ is a screening questionnaire and not a scale, Sadeh (48) did not provide a Cronbach’s α for the BISQ. Secondary outcomes for this study will include (1) nocturnal wakefulness, (2) sleep latency (the length of time it takes parents to put the infant to sleep in the evening, with responses captured as “less than 5 min,” “5–15 min,” “16–30 min,” “31–60 min,” and “more than 1”), (3) the longest consolidated sleep episode, and (4) parental perception of problematic infant sleep; these secondary outcomes will also be measured using the expanded BISQ. The expanded BISQ will be administered as part of a complete study online questionnaire package that includes questionnaires measuring covariates, in the 5–7 days before each of the baseline and outcome home visits. Outcome and covariate measures are presented in Tables 2 and 3. Demographic information, including (1) parental age, education, ethnicity, and income; and (2) infant age, birth order, and feeding type will be collected. At baseline and outcome, parents will be asked to describe the techniques, strategies, and resources that they use to promote infant sleep, which will be explored further during the qualitative interviews.

**Table 2 T2:** Measure for primary (frequency of night wakings) and secondary (nocturnal wakefulness, sleep latency, longest consolidated sleep episode, and parental perception of problematic infant sleep) outcomes.

Measure	Description
Expanded Brief Infant Sleep Questionnaire [BISQ; (48, 53)]	32-item questionnaire of infant sleep patterns, sleep ecology, and caregiver perceptions; responses include numerical (time, frequency), categorical (sleep location, bedtime activities), and ordinal rankings (how much of a problem is your baby’s sleep). No composite score is calculated. High 3-week test–retest reliability for sleep duration and wakefulness, night wakings, sleep-onset time, and settling time (0.82–0.95; 48). Used to assess sleep interventions for infants 6–36 months with a parent-identified sleep problem and detect significant short- and long-term improvements in the number of infant night wakings and sleep latency (49, 55, 56). Used in an internet sample (*N* = 4,505) of Canadian and United States parents of infants aged 0–36 months (53) and an international sample (*N* = 29,287) of parent of infants aged 0–36 months (57). Night wakings correlated with actigraphy, *r* = 0.42, and daily logs, *r* = 0.83 (48). Frequency of night wakings accounted for 13.27% of variance in parental perceptions of severity of sleep problems (53). Differentiated between clinical and control infants with two BISQ items, frequency of night wakings and nocturnal sleep duration, with assignment of cases to the correct group 85% of the time (48). Average completion time is 6.21 min (53)

**Table 3 T3:** Covariate measures.

Measure	Description
PCITS (34)	73-item binary measure of parent–child interactions on 4 parent (sensitivity to cues, response to distress, social-emotional, and cognitive growth fostering) and 2 child (clarity of cues and responsiveness to caregiver) subscales. Higher scores indicate higher quality interactions. Internal consistency for mothers, α = 0.53–0.87 (34) and fathers, α = 0.64–0.82 (58). Test–retest reliability (1 and 12 months) of 0.85 for caregiver and 0.55 for infant subscales (34). Concurrent validity with Home Observation Measure of the Environment scale (59). Predicts attachment, cognitive and language abilities (34, 60). Play session typically lasts 3–5 min
EPDS (61)	10-item measure of symptoms of depression, anxiety, and suicidal thoughts. Higher scores indicate more depressive symptoms. In mothers, correlated with Beck Depression Inventory second version, 0.82 (62). In fathers, EPDS was correlated with Center for Epidemiologic Studies Depression Scale, 0.62 (63). Internal reliability in mothers, α = 0.53–0.87 (62) and fathers, α = 0.87 (63); takes 3–5 min
IBQ-R very short form (64, 65)	37 statements of parental perception of infant temperament on 3 subscales: negative emotionality, positive affectivity, and regulatory capacity. Rated on a 7-point scale; higher scores indicate more difficult temperament. Internal reliability was 0.75–0.78 (65). Subscale test–retest reliabilities (2 and 12 months) from 0.64 to 0.88 (65). Mother–father inter-rater correlations from 0.28 to 0.61 for infants aged 4–6 months (65). Correlations with IBQ-R from 0.71 to 0.86; takes 12 min (65)
MCISQ (66)	20 items about parenting beliefs about infant sleep on 5 subscales: setting limits, anger, doubt, feeding, and safety; higher scores indicative of more negative concerns and doubts (66). Cronbach’s α = 0.82; 1-month test–retest = 0.81 (66). Mother–father correlations from 0.65 to 0.72 (67). Mothers’ scores (doubt) and fathers’ scores (anger) correlated with actigraphy (67). Overall score (mothers) and limit setting subscale (mothers and fathers) discriminated clinical and control groups (67); takes 5–10 min
DAS-4 (68, 69)	4 item measure of marital satisfaction; higher scores indicate stronger satisfaction. Internal consistency reliability (α = 0.84); temporal stability demonstrated using structural equation modeling over a 2-year period (69). Established discriminant validity for couple distress and predictive validity for couple dissolution (69). Used to assess relationship satisfaction in fathers (70), as well as in married and unmarried parents (71); takes 3–5 min
PSOC (72)	16-item measure with satisfaction, efficacy (72), and interest (73, 74) subscales; higher scores indicate higher parental competence. Internal reliabilities for satisfaction (0.75) and self-efficacy (0.76) subscales (72). Test–retest (6 weeks) for the total score and subscales ranged from 0.46 to 0.86 (72). Convergent with internalizing (−0.17 to −0.27) and externalizing (−0.10 to −0.31) behaviors on the Child Behavior Checklist (72) and marital satisfaction, 0.27 to 0.32 (75). Used to assess parental competence in mothers of children (0–4 years) with sleep problems (76); takes 3–5 min

*NOTE: Estimated time to complete questionnaire package is 36–57 min. PCITS, Parent–Child Interaction Teaching Scale; EPDS, Edinburgh Postnatal Depression Scale; IBQ-R, Infant Behavior Questionnaire—Revised; MCISQ, Maternal Cognitions about Infant Sleep Questionnaire; DAS-4, Brief version of the Dyadic Adjustment Scale; PSOC, Parental Sense of Competence*.

### Stepwise Procedure

#### Data Collection and Management

This community-based study will use both an online format and in-person home visits to collect baseline and outcome data (for a schedule of assessment, see Table 4) from both mothers and fathers separately. Families will be assigned a unique study identification number, which will be used to link mothers and fathers of the same family.

**Table 4 T4:** Play2sleep study schedule of enrollment, interventions, and assessments.

Study period						
	Enrollment	Baseline	Randomization	Initial visit	Outcome visit	Family interview
Time point	*−t*2	*−t*1	0	*T*1	*T*2	*T*3
**Enrollment**						
Eligibility screen	X					
Informed consent	X (verbal)			X (written)		
Allocation			X			
**Intervention**						
*Play2Sleep Group*				X		
*Comparison Group*				X		
**Assessments**						
*Expanded BISQ*		X			X	
*PCITS*				X	X	
*EPDS*		X			X	
*IBQ-R very short form*		X			X	
*MCISQ*		X			X	
*DAS-4*		X			X	
*PSOC*		X			X	
*Interview*						X

*BISQ, Brief Infant Sleep Questionnaire; PCITS, Parent–Child Interaction Teaching Scale; EPDS, Edinburgh Postnatal Depression Scale; IBQ-R, Infant Behavior Questionnaire—Revised; MCISQ, Maternal Cognitions about Infant Sleep Questionnaire; DAS-4, Brief version of the Dyadic Adjustment Scale; PSOC, Parental Sense of Competence*.

Online study questionnaires, hosted on Qualtrics, will be used to collect the majority of data on outcomes and covariates at baseline, when the infant is aged 5 months, and at outcome, when the infant is aged 7 months. Qualtrics is a recognized and secure electronic survey system that houses data on secure Canadian servers. Parents (mothers and fathers) in both groups will each complete baseline questionnaires in the 7 days prior to the initial home visit. A link to the baseline questionnaires will be emailed to parents 5–7 days before the home visit, and an email reminder encouraging parents to complete the questionnaires prior to the home visit will be sent if necessary.

The first home visit will occur when the infant is 5 months old (±2 weeks), at a time that is convenient to the family. [name] and colleagues (38) have demonstrated 5 months of age is a feasible time-point to begin a video self-modeled intervention. Scheduling the home visit when the infant is 5 months of age will allow sufficient time between referral to the study at the 4-month well-child clinic visit and scheduling of the first home visit. Scheduling the home visits within a 2-week window of 5 months provides a realistic timeframe to schedule visits based on availability of both parents, as well as being able to re-schedule visits if there are unanticipated events (i.e., infant illness). This narrow window minimizes maturation bias due to the rapid developmental changes that occur in infants at this age.

An automated randomization service (77) will generate the randomization sequence to allocate families to either the experimental or comparison group. Allocation concealment will be achieved because the randomization code will not be requested until the family enrolls in the study and parents complete the baseline questionnaire. After participants have completed the baseline questionnaire and immediately before the initial home visit, the home visitor will submit an online form requesting treatment allocation. A copy of the allocation will be emailed to the home visitor and stored in the study’s online Sealed Envelope Ltd. account.

At the start of the first home visit, participants will affirm their verbal consent (provided during the eligibility screening phone call) by providing written consent. After establishing initial rapport with the parents, the home visitor will ask each parent (mother and father) to teach their infant a unique age-appropriate play task, which is video-recorded by the home visitor to be coded later using the PCITS coding scheme (34). As per the PCITS manual, the video-taped structured teaching and play sequence lasts no longer than 10 min, typically spanning a 3- to 5-min timeframe (34). The order of the video-recordings will alternate between the mother and father to prevent ordering bias. Following the video-recorded structured play session, the home visitor will deliver either the Play2Sleep or comparison intervention. At the conclusion of the home visit, the home visitor will offer to schedule the outcome home visit.

The outcome home visit will occur when the infant is aged 7 months (±2 weeks). Seven months was selected because parents need time to practice and solidify new interaction patterns to translate into measurable effects on infant sleep patterns. Parents (mothers and fathers) in both groups will each complete outcome questionnaires in the 7 days prior to the second (outcome) home visit. During the outcome home visit, parents in both the experimental and comparison groups will again engage their infant in a different play task that is video-recorded for later coding. All families will be offered a listing of local infant sleep-related resources and services. Once data collection is completed, data will be downloaded, backed-up, and deleted from the Qualtrics account.

Following the home visits, a reliable coder who has achieved the required reliability of 90% with the PCITS training videos and who is blind to group allocation will code the videos. Coding of video-recorded interactions occurs at a later time and typically takes 30 min. A random selection of 10% of the videos will be re-scored to assess intra-rater reliability. Another reliable PCITS coder will rescore 20% of the videos to assess inter-rater reliability.

The same home visitor will interview families who are selected to continue to Phase 2 during a third home visit. Families from each group will be purposively sampled for maximum variation based on the change in the number of infant night wakings from baseline to outcome. Mothers and fathers will be interviewed as a family unit, rather than conducting individual interviews (78). Interviews will last up to 60 min and be digitally audio-recorded and transcribed verbatim. The semi-structured interview guides (Table S5 in Supplementary Material) include prompts that focus on capturing underlying relational and family processes in addition to eliciting individual family members’ perceptions and experiences (78, 79).

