## Ethics and Dissemination

### Informed Consent and Institutional Review Boards

This protocol and study, including the informed consent forms, have received ethical approval from the University of Calgary Conjoint Health Research Ethics Board (REB15-2652), and will be renewed annually.

Individual informed consent will be obtained from each parent by ensuring that they understand the study purpose, what participation in the study entails, as well as the potential risks and benefits of participating in the study. Consent forms will be written at the eighth grade reading level. The consent form will be reviewed with each parent verbally over the phone prior to enrollment, along with an electronic copy provided to each parent *via* email. At the first home visit, the home visitor will obtain signed copies of the consent form from each parent after providing participants an additional opportunity to review information, ask additional questions, or obtain further clarification as needed.

At each home visit (baseline and outcome), families will receive a thank-you card containing a $10 gift card in recognition of the time and effort that families have allocated to the study. Each family who participates in the qualitative interviews will receive an additional $10 gift card.

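### The home visitor learns the arm just before the first visit, so written consent and the baseline play recording (PCITS) are handled with allocation known, though the primary-outcome baseline is protected

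*Protocol article*

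**What the plan says.** The order of events is in the protocol article under Data Collection and Management, and Table 4 agrees with it.

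- Both parents give verbal consent at the screening call (Participants). The ethics section adds: "The consent form will be reviewed with each parent verbally over the phone prior to enrollment".
- Parents complete the online baseline questionnaires, including the expanded BISQ that carries the primary outcome.
- After that, and "immediately before the initial home visit, the home visitor will submit an online form requesting treatment allocation". The reply goes to the same person: "A copy of the allocation will be emailed to the home visitor".
- Written consent follows: "At the start of the first home visit, participants will affirm their verbal consent (provided during the eligibility screening phone call) by providing written consent". The ethics section names who takes it: "At the first home visit, the home visitor will obtain signed copies of the consent form from each parent".
- The home visitor then builds rapport, sets each parent a teaching task and films it for PCITS coding. Only afterwards do the arms part: "Following the video-recorded structured play session, the home visitor will deliver either the Play2Sleep or comparison intervention".

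Table 4 places allocation at time 0, and written consent and the first PCITS at T1. The Blinding section states that "the home visitor cannot be blinded to group", on the ground that one person delivers both interventions. PCITS videos are coded later by someone who does not know the group.

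**The concern.** Two steps that are the same in both arms, written consent and the baseline recording, are carried out by someone who already knows which intervention will follow. The reason given for not blinding the visitor applies from the moment the intervention is delivered. It does not explain why the arm must be known earlier.

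Two things are at stake. First, a family that does not sign at the visit is lost after randomisation, and the person handling that conversation knows the arm. The Sample Size section recruits until 60 families have complete data, so such a family would in effect be replaced, which sits uneasily with the intention-to-treat principle stated for the Phase 1 analysis.

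Second, and more important, the first PCITS recording is meant as a baseline. In the Play2Sleep arm the session has another purpose, because it must draw out infant disengagement cues for the feedback that follows. Its length is also flexible, usually three to five minutes with a cap of ten. A visitor who knows that feedback is coming has a reason, even unconsciously, to run the session differently. Blinded coding scores faithfully what was filmed; it cannot correct for how the session was conducted.

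**Working it through.** The plan gives no figure for this point, so the check is mainly a comparison of the stated sequence with the safeguards.

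**1. Which steps precede allocation?** Each step is placed using Data Collection and Management, Table 4 and the ethics section.

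| Step | Before or after allocation | Is the arm known to the visitor? |
|---|---|---|
| Phone review of the consent form, verbal consent of both parents | Before | No |
| Baseline questionnaires, including the BISQ | Before | No |
| Allocation requested and emailed | Time 0 | Becomes known |
| Written consent of both parents | After (T1) | Yes |
| Baseline PCITS recordings | After (T1) | Yes |
| Intervention delivered | After (T1) | Yes, unavoidably |

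Nowhere does the article say that the emailed allocation stays unopened until later in the visit.

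**2. What does the concealment argument cover?** The article rests concealment on requesting the code only after enrolment and the baseline questionnaire. That covers the first two rows. It does not cover written consent or baseline PCITS.

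**3. What does blinded coding cover?** It covers scoring. Setting up the task, building rapport and filming are done by the unblinded visitor.

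**4. What is PCITS used for?** Table 3 lists it as a covariate measure. It is neither the primary outcome nor one of the four secondary outcomes in Measures. Under Phase 1 Quantitative Analysis, correlations are used to pick potential covariates, covariate sub-analyses follow only if the primary outcome differs significantly between groups, and PCITS scores are compared with norms. Clinical Implications adds that the data should show which domains of interaction matter most for infant sleep.

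**5. How large is it?** The inputs are from Trial Status: 54 families enrolled at submission, 61 expected to be needed, 60 with complete data.

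- Families still to be enrolled: 61 − 54 = 7, or 7/61 = 11.5% of the expected total.
- Expected loss from all causes: 61 − 60 = 1, or 1/61 = 1.6%.
- Weight of a single family in the target sample: 1/60 = 1.7%.

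The second figure includes every reason for incomplete data, so a loss specific to written consent can only be part of it. The count of 7 is approximate, because some of the 54 enrolled may not yet have had their first visit.

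**The case against.** The strongest reply has four parts.

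**Consent was already given.** Both parents consent verbally before allocation, after a phone review of the form, and the visit signature affirms that consent. A reader might infer from the sequence that concealment at entry failed, or that parents consent knowing their arm. The documents do not support either. Only the visitor is said to receive the allocation, and parents are described as partially blinded. This part stands, and it limits the consent exposure to the written step.

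**PCITS is peripheral.** A reader might infer that the trial's main result, or an analysis of change in PCITS, is compromised. The primary-outcome baseline is collected before allocation, and the analysis section describes no change-from-baseline analysis of PCITS. This also stands.

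**The session is standardised.** It follows the PCITS manual with a time cap, the order of parents alternates, the coder is blinded and trained to 90% reliability, and 10% and 20% of videos are re-scored for intra-rater and inter-rater reliability. The Limitations section already admits that an unblinded single visitor may bias outcomes. These safeguards reduce the risk, but none removes the visitor's knowledge while the session is being run.

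**The arm may be needed sooner.** It is tempting to say that nothing requires the arm until both recordings are finished. The description of the Play2Sleep arm places the review directly after the play session, with each parent separately, and times play and review together for each parent. That can be read as one parent's play and review, then the other's. On that reading the arm is needed after the first recording. Data Collection and Management can be read the other way. The point stands as a caution: the change may require a small re-ordering of the visit.

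**Conclusion.** The concern holds in a limited form. The visitor knows the arm when taking written consent and when conducting the baseline PCITS session, and the second is the weightier exposure. The initial enrolment decision and the primary-outcome baseline are not affected.

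The size is modest. Every family handled in this order has its baseline PCITS recorded by someone who knew the arm, but the direction and amount of any distortion cannot be derived from the documents, and they show no differential conduct or consent loss. Loss from all causes is expected to be about 1 family in 61. The point does not invalidate the primary comparison; it is an avoidable weakness that can be removed cheaply.

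The conclusion assumes that visits follow the written sequence, and that the visitor reads the emailed allocation before arriving.

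**What to change.** For families not yet visited (about 7 of the anticipated 61), request or open the online allocation only after both parents have signed and both baseline play recordings are made. If play and review were meant to run parent by parent, record both parents before any video review begins.

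For families already enrolled:

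- report, by arm, any family that was allocated but did not sign;
- keep those families in the randomised count of the CONSORT flow diagram;
- state that baseline PCITS was recorded by a visitor who knew the arm.

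The cost is a procedural note and a data connection in the home. The visitor can no longer plan the visit length by arm (about 1.5 h against about 1 h), and the first parent's review may be slightly delayed.
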